#### Incentives

Participants will not be offered incentives to undertake the intervention, other than receipt of free, evidence-based mental health care. Those participants who are also students enrolled in first-year psychology courses will receive course credit for their participation in the program. To improve attendance at Module 5, where post-program assessments are conducted, all participants will be offered either a coffee or supermarket voucher (AUD$15 value) for attendance. To minimise attrition, participants will be offered AUD$50 incentive to complete each of the 6-month and 12-month follow up assessments. Participants will be followed up unless they actively withdraw from the trial (i.e., data will be sought from participants who did not attend group sessions or who no longer meet inclusion criteria, in order to honour the intention-to-treat principle).

### Randomisation

Participants who are eligible will be randomly assigned by the research team following simple randomisation procedures (computerized random numbers using Excel random number generator feature) to either G4H or CBT using a 1:1 ratio. Participants will be randomised at the group level once sufficient participants have been recruited for a group (minimum of 5). That is, participants will first be recruited into a treatment group, and each group will then be randomised to receive either G4H or CBT, using the randomisation process outlined above. Neither the participant nor the research team will be blind to intervention status. Assessment of primary outcomes at each timepoint will occur via a web interface to ensure that this is not affected by intervention status.

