## Method

### Trial design

CARR is a two-arm non-inferiority parallel (1:1 ratio) randomised controlled trial. A summary of this study’s compliance with Standard Protocol Items: Recommendations for Interventional Trials (SPIRIT), is provided in the Additional file 1.

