### Participants

Participants will be 200 young people presenting with psychological distress recruited from two sources in South East Queensland, Australia: (1) a community youth mental health service (headspace, five sites), and (2) a university psychology clinic (University of Queensland). The following criteria will be used in recruitment:

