### Intervention

Participants will be randomly assigned to receive either G4H or CBT. Groups will not commence unless a minimum of 5 people have consented to participate, with the maximum number of people recruited to each group being 9 people. Interventions are matched for contact time and mode of delivery, and both include five group sessions of 60–90 min in duration, run weekly for the first four weeks, and a final “booster” session that is held one month later. Postgraduate students in professional psychology (with provisional registration) will facilitate the groups (2 facilitators per group). Treatment fidelity and consistency of program delivery will be maintained by providing: a half-day of training, weekly group supervision from a registered clinical psychologist, direct observation by investigators to ensure quality, and regular team meetings with the research team. Additionally, G4H facilitators will anonymously complete a brief questionnaire at the end of each session to assess (a) what session activities were covered, (b) the length of session, and (c) facilitator session satisfaction and ease of delivery. Facilitators will also record participant attendance.

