### Sample size power calculations

The CARR sample size was determined by power calculations for a non-inferiority trial, using effect sizes and retention rates from our published pilot study. We have estimated the non-inferiority margin based on historical evidence for the effect size of the active comparator (based on recommendations by [46] and [47]). The effect size of this CBT program versus control was *d* = 0.49 at 6 month follow up (recalculated from [28] using methods recommended by [19]). This corresponds to 2.2 points on the DASS-21 depression subscale (using the expected standard deviation for an adolescent population of 4.53; [31]). To have 0.80 power to detect this difference with an alpha level of 0.05*,* 67 people per condition would need to be retained at follow up. Assuming 50% eligibility and 67% survival rates, which are consistent with our pilot data, we anticipate that screening 400 people for eligibility (see Fig. 2) will lead to retention of *N* = 67 per condition at follow up [48]. However, this is a conservative estimate of retention due to the addition of incentives for follow up data completion in this trial [49].

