### Analyses

Data quality will be improved by using a web interface that prompts (but does not force) participants to complete missing items. This will reduce missing data and prevent errors from manual data entry. Data quality will be checked by assessing ranges for each variable and interrogating outliers. We will examine the differences in baseline characteristics between the groups descriptively. Since differences between randomised groups at baseline could have occurred by chance, no formal significance testing will be conducted (in accordance with recommendations by [50]). No covariates will be included in the primary analysis (in accordance with recommendations by [51]). However, we will include exploratory analyses which assess the interaction between condition and baseline characteristics where indicated.

To assess the effect of intervention, group differences on the primary and secondary outcome measures, with all available timepoints included in the model, will be examined using a series of mixed effects repeated measures (MMRM) models, which will specify timepoint, participant, and therapy group as levels in the analyses. MMRM is a full information maximisation likelihood estimation strategy that can model data even when some observations are missing, and thus honours the intention-to-treat principle [52]. For all hypothesis testing, both intention-to-treat analyses (ITT; where all available data are included in MMRM) and per protocol analyses (PP; only including participants who met eligibility criteria throughout the trial period, were randomly assigned, completed the intervention according to the protocol, and had both baseline and follow up data) will be completed. Best fit, as determined by Information Criteria (e.g. AIC; BIC) method will be used for determining the covariance structure for MMRM models.

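### Simple randomisation of only 23 to 40 therapy groups does not secure equal arms or balance between the two recruitment services; stratified blocks would do so at almost no cost

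*Protocol article*

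**What the plan says.** The Trial design section states that "CARR is a two-arm non-inferiority parallel (1:1 ratio) randomised controlled trial". The Randomisation section says that assignment is made "following simple randomisation procedures (computerized random numbers using Excel random number generator feature"). It then makes the therapy group the unit: "each group will then be randomised to receive either G4H or CBT, using the randomisation process outlined above". It mentions no block, stratum or other restriction.

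The Intervention section sets a lower bound on group size: "Groups will not commence unless a minimum of 5 people have consented to participate". The same section sets the upper bound at 9 people per group.

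The Participants section gives a total of 200 and two sources: "1) a community youth mental health service (headspace, five sites), and (2) a university psychology clinic".

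The Sample size power calculations section concludes that "67 people per condition would need to be retained at follow up".

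The Analyses section says "No covariates will be included in the primary analysis". Its mixed model has timepoint, participant and therapy group as levels. Service and site are not named, and baseline characteristics enter only exploratory interaction analyses.

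**The concern.** Simple randomisation relies on large numbers to even out the arms. That works for several hundred individuals, but the units here are a few dozen groups, each carrying 5 to 9 people. One extra group in an arm moves several participants at once, so lopsided arms are common. The sample size has no stated allowance for this, because 67 per condition is 67% of exactly 100.

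The same applies to service. A community youth mental health service and a university clinic may draw different young people, and nothing in the allocation or the primary model keeps their shares similar across arms. At stake are some precision and the credibility of the single realised comparison, should one arm turn out mostly headspace and the other largely university clinic.

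**Working it through.** **Inputs from the protocol article.** N = 200 (Participants); group size 5 to 9 (Intervention); margin 2.2 points, SD 4.53, power 0.80, alpha 0.05, 50% eligibility and 67% retention (Sample size power calculations).

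**The plan's own figure.** With two-sided 0.05, n per arm = 2 × (1.96 + 0.84)² × 4.53² / 2.2² ≈ 66.6, so 67. Retention: 400 × 0.50 × 0.67 / 2 = 67. Both routes reproduce the stated figure, and the second uses exactly 100 per arm.

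**Number of units.** 200/5 = 40 at most. 200/9 = 22.2, and 22 × 9 = 198 is below 200, so at least 23.

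**Realised split.** The number of groups in one arm is Binomial(K, 0.5). The table takes groups of equal size.

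| K | P(equal number of groups) | 60:40 or worse means | Probability | SD of participants per arm |
|---|---|---|---|---|
| 23 | 0 (odd) | 9:14 | 0.40 | 20.9 |
| 28 | 0.15 | 11:17 | 0.34 | 18.9 |
| 40 | 0.13 | 16:24 | 0.27 | 15.8 |

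At 67% retention the smaller arm is below 67 whenever the split is not exactly equal. That has probability 0.85 with 28 groups and 0.87 with 40, and is certain with 23. The expected number retained in the smaller arm is about 56 to 59. With group sizes drawn uniformly from 5 to 9 (mean 29 groups), P(80:120 or worse) is 0.31.

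**Power.** Power = Φ(2.2 / [4.53 × √(1/n₁ + 1/n₂)] − 1.96) with n₁ + n₂ = 134. Like the plan's own calculation, this ignores clustering.

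| Randomised | Retained | Power |
|---|---|---|
| 100:100 | 67.0 : 67.0 | 0.803 |
| 90:110 | 60.3 : 73.7 | 0.799 |
| 80:120 | 53.6 : 80.4 | 0.786 |
| 70:130 | 46.9 : 87.1 | 0.765 |
| 60:140 | 40.2 : 93.8 | 0.731 |

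Averaged over the randomisation, power is 0.784 (K = 23), 0.787 (K = 28) and 0.792 (K = 40). Power below 0.75 has probability 0.09, 0.09 and 0.04.

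**Service share.** The article does not give the clinic's share of groups. I assume 30 to 50%, and that each group comes from one service. Entries are the probability that the clinic share differs between arms by at least the stated gap.

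| K | At least 20 points | At least 30 points |
|---|---|---|
| 23 | 0.31–0.41 | 0.14–0.21 |
| 28 | 0.26–0.35 | 0.09–0.11 |
| 40 | 0.19–0.27 | 0.05–0.08 |

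**What such a gap can do.** The shift in the contrast is the gap in share multiplied by the difference between services in mean change. If that difference were 3 points (an assumption for illustration), a gap of 20 to 30 points would shift the contrast by 0.2 × 3 = 0.6 to 0.3 × 3 = 0.9 points. To shift it by the whole margin, the services would have to differ in change by 2.2/0.2 = 11 points or 2.2/0.3 = 7.3 points, on a subscale whose maximum is 7 × 3 = 21. To shift it by one standard error, 4.53 × √(2/67) = 0.78, they would have to differ by 3.9 or 2.6 points.

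**With the fix.** Permuted blocks of four stratified by service, with 30% of groups from the clinic and equal group sizes, give 100:100 at K = 28 and K = 40 (power 0.803), where both strata fill whole blocks. At K = 23 the worst split is about 96:104 (64 retained in the smaller arm, power 0.802). A stratum ending on an incomplete block of four can leave the arms up to two groups apart.

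**The case against.** Simple randomisation is valid and is the one method with no predictability, which matters because the Randomisation section has an unblinded research team doing the assigning. The 1:1 ratio is met as an allocation probability. The larger arm compensates for most of what the smaller one loses, so the average cost is 1 to 2 points of power, and the article calls its retention figure conservative because follow-up incentives were added. Leaving out covariates is a deliberate choice that cites a recommendation. All of this stands, and it limits the size of the point.

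Three stronger readings are tempting and are not supported:

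- **That service imbalance biases the comparison or passes straight into it.** Imbalance arising by chance from a valid randomisation is not bias. The between-arm tests are condition-by-time interactions, the margin is on change scores, and baseline is a modelled timepoint. A stable level difference between services therefore cancels, and only a difference in change over time reaches the contrast. The article reports no such difference. Course credit goes to first-year psychology students without being tied to either service, so it does not establish one.
- **That imbalance could mimic or hide a difference the size of the margin.** At the gaps considered, this needs the services to differ in change by 7.3 to 11 points.
- **That the services will be unbalanced.** Balance is left to chance. Under the assumed shares, a gap of 20 points or more is avoided more often than not.

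The predictability objection stands only in part. Participants are recruited into a group before it is allocated, so blocks of varying size give little to exploit, provided that the allocation stays concealed until membership is closed.

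**Conclusion.** The point holds as a cheap improvement to a method that the article states outright. Unrestricted allocation of 23 to 40 groups leaves a 60:40 or worse split with probability of about 0.27 to 0.40. It makes 67 retained in both arms unlikely at the planned retention, and it leaves the service mix to chance, with a 20-point or larger gap in about 0.19 to 0.41 of allocations. The average loss of power is 1 to 2 points while the total stays at 200, and a fall below 0.75 is a minority outcome. The service imbalance costs precision and credibility. The therapy-group level in the model neither balances nor adjusts for service.

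The figures rest on equal-sized groups (except where group sizes were drawn at random), 67% retention, the individual-level variance used in the plan, and an assumed clinic share of 30 to 50% of groups.

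**What to change.** Generate the allocation list before recruitment, in permuted blocks of groups with randomly varying block size, stratified by service (headspace or university clinic). Conceal it, and release each allocation only after the membership of that group is closed. Add service and service-by-time as fixed effects to the primary model, and amend the no-covariate sentence to allow this stratification factor. Stratifying further by the five headspace sites would leave strata too thin for so few groups.

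The cost is a new list for groups not yet allocated and a sentence each in the randomisation and analysis text. The downsides are slight predictability at block ends with an unblinded team, and about one or two degrees of freedom at the group level for the contrast at a given timepoint.

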#### Exclusion

Currently in receipt of other evidence-based treatment for depression (psychotherapy or psychopharmacology)Current high risk suicidal ideation or severe self-harming behaviour.Current psychotic episode or severe personality disorder that would interfere with ability to participate in group work.Severe neurological condition or severe learning impairment that would hinder engagement with the content of the proposed interventionsCurrent alcohol or other substance dependence / intoxication

Participants will be monitored throughout the trial for any change in these inclusion and exclusion criteria (e.g., in adjunct treatment status, or in suicide risk). Participants whose mental health declines for any reason will be provided with additional one-on-one supportive counselling by their group facilitator and referred to additional treatment where indicated. If a person who is initially eligible for the trial subsequently meets an exclusion criterion at any point during the active-treatment phase of the trial (T0-T5) they will be excluded from per-protocol analyses, but not intention-to-treat analyses.

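### The article declares the whole research team unblinded and describes no masked step for per-protocol membership, outlier queries or the covariance choice; masking these before arm codes are revealed is a cheap improvement

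*Protocol article*

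**What the plan says.** The Randomisation section is explicit: "Neither the participant nor the research team will be blind to intervention status". The safeguard it offers concerns data collection: "Assessment of primary outcomes at each timepoint will occur via a web interface to ensure that this is not affected by intervention status".

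Per-protocol membership is defined in two places. Under Exclusion, participants who come to meet an exclusion criterion between T0 and T5 are dealt with as follows: "they will be excluded from per-protocol analyses, but not intention-to-treat analyses". One of those criteria reads: "Current psychotic episode or severe personality disorder that would interfere with ability to participate in group work". Under Analyses, the per-protocol set also requires that participants "completed the intervention according to the protocol, and had both baseline and follow up data".

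On data checking, the Analyses section says: "Data quality will be checked by assessing ranges for each variable and interrogating outliers". It adds that the covariance structure of the mixed model will be the best-fitting one by information criteria, with AIC and BIC given as examples. Intention-to-treat and per-protocol analyses are both to be run for every hypothesis. The non-inferiority margin is 2.20 points on the DASS-21 depression subscale.

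**The concern.** Participants and facilitators cannot be masked to a talking therapy. The people who sort participants into analysis sets, query odd values and choose the covariance structure can be masked, at least in part. As worded, the article rules this out for the whole team without distinction.

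That matters because some of these decisions need judgement: whether a condition is severe, whether it would interfere with group work, and whether someone completed the intervention as the protocol intends. If they are settled with arm and outcome in view, the per-protocol estimate is open to unconscious selection. That estimate is one of the two analyses of the non-inferiority hypothesis. Collecting outcomes online protects the answers given, but not what is later done with them.

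**Working it through.** **1. Which decisions are open, and what they feed**

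| Decision | What the article fixes | What it leaves open | Feeds |
|---|---|---|---|
| Per-protocol membership | Exclusion criterion met in T0–T5; completion; baseline and follow-up data present | Severity and interference; what counts as completing (no session count) | Per-protocol only |
| Outliers | Ranges checked, outliers looked into | Threshold and resulting action | Per-protocol and ITT |
| Covariance structure | Best fit by an information criterion | Which criterion; which candidate structures | Per-protocol and ITT |
| Rest of the primary model | Mixed model; levels for timepoint, participant and therapy group; no covariates | Not at issue here | Both |

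No section describes masking for the first three rows, and none names the person responsible. The relevant sentences are in the passive.

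**2. The plan's own figure**

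Inputs from the sample size section: margin 2.2, SD 4.53, power 0.80, alpha 0.05 (sidedness not stated).

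n per arm = 2 × (1.960 + 0.842)² × 4.53² / 2.2² = 66.6, rounded up to 67.

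This reproduces the stated 67 with a one-sided 0.025 test and a true difference of zero. A one-sided 0.05 test gives 53 and does not. The flow agrees: 400 × 0.50 = 200 eligible, and 200 × 0.67 / 2 = 67 per arm. Masking does not alter this number.

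**3. An illustrative scale**

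Assumptions: 67 per arm, SD 4.53, independent observations (no clustering by therapy group), and non-inferiority judged by the upper limit of a two-sided 95% interval against 2.20.

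- SE = 4.53 × √(2/67) = 0.783.
- Half-width = 1.96 × 0.783 = 1.53.
- Largest observed difference that still meets the margin = 2.20 − 1.53 = 0.67.

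Suppose k G4H participants scoring c SD worse than their arm mean are left out of the per-protocol set. The arm mean then moves by k × c × 4.53 / (67 − k). The last column takes a true difference equal to the margin and keeps SE at 0.783: chance of wrongly concluding non-inferiority = 1 − Φ(1.96 − shift/SE).

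| k | Shift, c = 1 to 2 | Chance of false non-inferiority (nominal 0.025) |
|---|---|---|
| 1 | 0.07 to 0.14 | 0.031 to 0.037 |
| 3 | 0.21 to 0.42 | 0.046 to 0.078 |
| 5 | 0.37 to 0.73 | 0.068 to 0.152 |

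Both k and c are assumptions; the article gives no figure for either. The table shows only that a handful of exclusions, all in one arm and one direction, would be large relative to the 0.67 available.

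**4. What masking can and cannot remove**

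Under the Exclusion section, participants who decline are referred for further treatment where indicated, and receiving other evidence-based depression treatment is itself an exclusion criterion. People who do worse may therefore leave the per-protocol set by rule, whoever applies it. Only the part of a shift that comes from borderline calls made with arm and outcome visible can be attributed to lack of masking.

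**The case against.** The case against is substantial, and much of it stands.

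- **Who decides.** A reader might infer that the unblinded team makes all these decisions. That is plausible, but the article does not say so.
- **How much of the model is open.** A reader might infer that the form of the model is up for choice. It is not: only the covariance structure is open, and a numerical criterion leaves less room than a free choice.
- **Interactions.** The analyses intended to "assess the interaction between condition and baseline characteristics where indicated" are labelled exploratory and do not enter the non-inferiority test.
- **Outliers.** Looking into outliers is presented as a data-quality check. The article does not say that values will be removed, and ITT is to use all available data.
- **ITT runs alongside.** It does not depend on per-protocol membership, so a distorted per-protocol result would have to differ from it. This limits the per-protocol route, but not the outlier or covariance routes.
- **Unseen documents.** A full protocol or statistical analysis plan may provide for masked review, and its absence from an article would not by itself be a finding. But the article goes further than silence. It states that the research team is not blind, without exception, so a masked step elsewhere would have to depart from that sentence.
- **Limits of masking.** Facilitators record attendance and know the arm, and whole groups are randomised, so masking will be imperfect. This reduces the benefit without removing it.

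**Conclusion.** The point holds as a cheap improvement. The article declares the whole team unblinded and describes no masked step for three decisions that are partly left to judgement. All three feed the per-protocol analysis of non-inferiority, and two also feed ITT. This rests on reading the research team as including those who prepare and analyse the data, which is the natural reading because no exception is made.

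Its size is not known. The shifts worked out above depend on assumed, one-directional exclusions and on ignoring clustering; they are a scale, not evidence of harm. A reader might infer that the non-inferiority conclusion is compromised or that selective exclusion is to be expected. The documents support neither. They show no wrong figure and no invalid primary method, and the ITT analysis gives a check on the per-protocol set.

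**What to change.** **Randomisation section.** Limit the statement on blinding to participants, facilitators and staff who recruit or supervise.

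**Analyses section.** Add that, before arm codes are revealed:

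1. per-protocol status is classified from attendance and eligibility records with arm identifiers and outcome scores removed. The session questionnaire should stay out of this file, because it is described for G4H facilitators only and would disclose the arm;
2. outliers are queried on a file with arm removed but outcome values visible, since an outlying score cannot be resolved unseen;
3. one information criterion and its list of candidate covariance structures are fixed, then applied on arm-coded data;
4. these decisions are dated and locked.

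If a fuller plan already provides for this, correcting the Randomisation sentence and referring to that plan is enough.

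**Cost.** Minor data-management work and slightly later unblinded outputs. The sample size and visit schedule do not change. Masking will remain imperfect, because facilitators know the arm and whole groups are allocated together.
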